### Interim analyses {21b}

No interim analyses are planned. Data collection will cease once the sample size has been achieved.

### Methods for additional analyses (e.g. subgroup analyses) {20b}

No additional analyses are planned. Subgroup analyses based on a stratified sample (i.e. between medical or psychiatric status or different demographic criteria) may be considered depending on the size and composition of the final sample.

### Methods in analysis to handle protocol non-adherence and any statistical methods to handle missing data {20c}

All data will be analysed using an intention-to-treat study design, regardless of protocol adherence. Missing responses within partially completed surveys will be handled as per the instructions in the scoring manual for each individual survey. Where timepoint data is missing, linear mixed model analysis will retain all data, and missing data will be assumed to be missing at random.

### Plans to give access to the full protocol, participant-level data, and statistical code {31c}

De-identifiable participant data will be stored in the University of Queensland data repository (UQRDM).

## Oversight and monitoring

### Composition of the coordinating centre and trial steering committee {5d}

The trial steering committee will consist of independent clinical members of the Catherine’s House Leadership team: the Medical Director, Nurse Unit Manager, Operational Manager, Allied Health Lead, Senior Peer Worker, Mental Health Information Manager, and Service Development and Research Team Leader. This group will meet approximately once a month.

### Composition of the data monitoring committee, its role and reporting structure {21a}

The study will designate a data monitoring committee (DMC) consisting of a minimum of four members of the Catherine’s House Leadership Team with expertise in statistical analysis, research ethics, and mental health. The DMC will meet monthly to oversee data quality, withdrawal or attrition information, and any adverse events. Access to the data will be monitored by a nominated data custodian.

### Adverse event reporting and harms {22}

All women will remain under the care of their usual treating doctors and maternity care clinicians, who will assist the women should any distress or discomfort arise. Participants will also be encouraged to inform the research team or contact one of the support service numbers listed in the information sheet, should they experience any physical or mental distress or harm for any reason while they are taking part in the research study.

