### Criteria for discontinuing or modifying allocated interventions {11b}

Participants will be free to withdraw from the study at any time. Women who appear in distress will be flagged by the research team, removed from the study, and offered additional support. To ensure the validity of results, all data collected from participants up to the point of withdrawal will be included in the analysis, which will be conducted according to the intention-to-treat principle.

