### Provisions for post-trial care {30}

The data collected in this study is not expected to cause significant distress or discomfort to participants. However, in the event that participants experience distress in the course of this study, the participant information sheet will provide participants with information about support services they can contact. This will include Beyond Blue, Lifeline, and the research team. In addition, participants who score highly on the EPDS scale, or noted on this scale that they have thought of self-harm, will be flagged by the research team, and further support will be offered.

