### Outcomes {12}

Postnatal depression will be the primary outcome of the study. This will be measured using the Edinburgh Postnatal Depression Scale (EPDS). The primary outcome will be EPDS measured at 6 months postpartum. Changes in postnatal depression over time will also be assessed and will be determined by conducting the EPDS at four timepoints: 16 weeks’ gestation, 28 weeks’ gestation, 3 months postpartum, and 6 months postpartum. Secondary outcomes measured at the same timepoints will include measures of mother-infant bonding (using the *Mother-to-Infant Bonding Scale*), quality of life, and cost-effectiveness (using the *PROMIS Global-10*). The primary timepoints for these assessments will be timepoint 1 (16 weeks’ gestation) and timepoint 4 (6 months postpartum). Mindful attention (using the *Mindful Attention Awareness Scale*) will be measured at times one and four. Participant satisfaction with the app (using a bespoke survey described below) will be measured at the third timepoint (3 months postpartum), and participant adherence (measured with click analytics to detect the frequency of app use) will be examined once participants have completed the study (see Fig. 1). The study will also use click analytics to determine the frequency of app use. Demographic data and medical health information will be extracted from medical records for the purposes of inferential statistical analyses. Changes from timepoint 1 will be assessed for all health-related, repeated surveys. Measures will be analysed in aggregate form.

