## Assignment of interventions: blinding

### Who will be blinded {17a}

Care providers will not be aware of the assignment status of participants. Trial participants will not be blinded to their group allocation status. A member of the research team, not involved with patient care, recruitment, or group allocation, will email the intervention group instructions for downloading the online app and will provide technical assistance to participants. The data analyst will be blinded to participant allocation.

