#### The Edinburgh Postnatal Depression Scale (EPDS)

The EPDS is a 10-item questionnaire designed to screen women for symptoms of depression in the postnatal period [25]. Women completing the EPDS are asked to rate the option that best describes how they have felt in the past 7 days in response to a number of statements (e.g. “I have blamed myself unnecessarily when things went wrong.”). Items are scored on a 4-point scale, with response scores ranging from 0 to 3. Item scores are summed to produce a total score. Scores ranging from 0 to 9 indicate low levels of distress, scores from 10 to 12 indicate the presence of distress, and scores above 13 suggest a high presence of depressive symptoms. A minimum 4-point change in scores across timepoints is necessary to be deemed clinically significant [26]. The EPDS has been validated for use in both a prenatal and postnatal population [25, 27]. Women who score one, two, or three on item 10 (“The thought of harming myself has occurred to me”) will be addressed with further enquiry and support if necessary [28].

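### The harms section states only spontaneous adverse event reporting in an open-label trial, and does not link the EPDS flags and distress removals from both arms to the DMC's review or to a comparison by arm

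*Protocol article*

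**What the plan says.** All references are to the protocol article.

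- **Adverse event reporting and harms {22}.** Usual clinicians look after women who become distressed. "Participants will also be encouraged to inform the research team or contact one of the support service numbers listed in the information sheet". The section describes no scheduled question about harms and no path from clinicians or support lines back to the trial.
- **Data monitoring committee {21a}.** "The DMC will meet monthly to oversee data quality, withdrawal or attrition information, and any adverse events".
- **Blinding {17a}.** Participants know their allocation. A team member "will email the intervention group instructions for downloading the online app and will provide technical assistance to participants".
- **Outcomes {12}.** Change in the primary outcome is followed by "conducting the EPDS at four timepoints: 16 weeks’ gestation, 28 weeks’ gestation, 3 months postpartum, and 6 months postpartum". Trial design {8} applies this four-visit schedule to all participants.
- **Post-trial care {30}.** Women with high EPDS scores or thoughts of self-harm "will be flagged by the research team, and further support will be offered".
- **EPDS instrument section.** Women who score 1, 2 or 3 on item 10 "will be addressed with further enquiry and support if necessary".
- **Discontinuation {11b}.** "Women who appear in distress will be flagged by the research team, removed from the study, and offered additional support".

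**The concern.** The harms section relies on a woman deciding to tell the team, and a call to an outside helpline is an equally acceptable response. In an open-label trial, that decision can depend on the arm. The app arm has instructions sent by a named function of the team and technical help to go with the app, so its women may report more readily. The opposite is also possible, if controls who missed the app are more inclined to report distress. The documents do not settle the direction.

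The trial also holds information that does not depend on volunteering and is gathered on one schedule in both arms: item 10 answers, EPDS totals and team-initiated removals. The text uses these to trigger support. It does not say that they are logged as adverse events, passed to the DMC as such, or tabulated by arm. A harms summary built from {22} alone would use the source most open to reporting bias and leave the less biased ones aside. This matters because the abstract describes the risks as low and the Discussion foresees use in more vulnerable women.

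**Working it through.** **1. The plan's own figure.** Sample size {14} gives d = 0.50, 80% power, two-sided 5%, 1:1 allocation and 40% attrition.
- Normal approximation: 2 × (1.960 + 0.842)² / 0.50² = 62.8, so 63 per arm, 126 in all.
- Exact t-test: 63.77, so 64 per arm, 128 in all, with power 0.801.
- Inflation: 128 / (1 − 0.40) = 213.3, so 214, or 107 per arm.

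Both 128 and 214 reproduce. The article states no harm rate, so the rest is a comparison of passages plus illustrations under labelled assumptions.

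**2. The harm sources side by side.**

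| Source | Needs a volunteered report? | Stated use | Stated link to DMC or harms comparison |
|---|---|---|---|
| Reports to team {22} | Yes | None beyond help | DMC reviews adverse events {21a} |
| Item 10 score of 1 to 3 | No, scheduled survey | Enquiry and support | None |
| High EPDS score {30} | No, scheduled survey | Support | None; total score is compared by arm as an outcome {20a} |
| Removal for distress {11b} | No, team decides | Support | Through withdrawal information {21a}; no recording of reasons stated |
| Medical records {12} | No | Inferential analyses | None; stillbirth or infant death appears only as a covariate {20a} |

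Only the first row is described as adverse event reporting, and it is the only row that depends wholly on the participant.

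**3. How much scheduled information there is.** With 214 women and full retention, item 10 yields 4 × 214 = 856 answers, of which 3 × 214 = 642 come after baseline. If instead only 128 women remain and all losses fall straight after baseline, the post-baseline count is 3 × 128 = 384. The planned range is therefore 384 to 642.

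**4. What unequal reporting could do (assumed rates).** Apparent risk ratio = true risk ratio × (reporting in app arm / reporting in control arm). With a true risk of 10% in both arms and 107 women per arm:
- 60% v 40%: 6.4 v 4.3 expected reports, ratio 1.5.
- 60% v 30%: 6.4 v 3.2, ratio 2.0.
- 80% v 40%: 8.6 v 4.3, ratio 2.0.
- Equal reporting at any level: ratio 1.0.

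In the other direction, reporting of 30% v 60% would make a true doubling look like 2.0 × 0.5 = 1.0.

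**5. What complete counting would and would not buy.** With zero events in n women, the exact one-sided 95% upper bound is 1 − 0.05^(1/n): 4.6% at n = 64, 2.8% at n = 107. Power to detect 5% v 10% is 19% with 64 per arm and 28% with 107; for 10% v 20% it is 35% and 54%. The abstract gives 360 participants; at 180 per arm the bound is 1.7% and the two powers are 44% and 76%. Complete counting reduces bias; it does not make the trial large enough for uncommon harms.

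**6. The flag itself.** {30} gives no number for a high score. The EPDS section gives bands of 0 to 9, 10 to 12 and above 13, which leave a score of 13 unassigned. A count of high scores is not reproducible until these passages are reconciled.

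**The case against.** The strongest objection is that other routes exist. The team flags and removes distressed women without waiting for a report, and the DMC reviews withdrawals monthly. The team reads EPDS flags from scheduled surveys. EPDS totals are compared by arm at 6 months and over time in a mixed model, so a worsening of the mean would show in the final analysis. The support contacts listed in {30} include the research team. All of this stands. A reader might infer that harms reach the DMC only when women volunteer them, or that the flags are withheld from it. The first is contradicted by {11b} and {21a}; the second is an inference from silence.

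A reader might also infer that the trial is planning a low-risk conclusion that it cannot support. The abstract's remark on risk is an assertion, and Objectives {7} lists no safety objective. Nor does "No additional analyses are planned" rule out a harms table, since it stands under subgroup analyses {20b}.

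Next, this is a condensed article, and definitions, forms and harm tables usually sit in the full protocol or analysis plan. That is a fair reason not to criticise their absence. It does not cover the route that {22} does state, which is passive in a trial without participant blinding.

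Finally, monthly by-arm tables of EPDS thresholds would be repeated looks at the primary outcome, while {21b} plans no interim analyses and the DMC comes from the same leadership team as the steering committee. This objection stands and shapes the fix.

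Against the reassurance from mean EPDS: it is seen only at the end, a mean can conceal a few women with self-harm responses, and women removed for distress contribute no later scores.

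**Conclusion.** The point holds in a limited form. As written, {22} names spontaneous reporting as the source of adverse events in a trial whose participants know their arm. The item 10 answers, high-score flags and distress removals have no stated link to the adverse events the DMC reviews or to a between-arm harms comparison. A summary built on {22} alone would be exposed to unequal reporting. An apparent ratio of 1.5 to 2.0 with no true difference follows from the assumed reporting pairs; the real reporting rates are unknown and could be equal. The primary analysis is not affected. This is a cheap improvement to how harms are counted, and it would not give the trial adequate power for uncommon harms.

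**What to change.** Amend {21a} and {22} as follows.

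1. Log as monitored harms: item 10 scores above 0; high EPDS flags, once the cut-off is reconciled between {30} and the EPDS section; removals under {11b}, with reasons; and serious maternal or infant events from the medical records already accessed. How removal in {11b} relates to the offer of support in {30} also needs reconciling.
2. Give these to the DMC at its existing meetings, pooled across arms. Do not supply routine by-arm tables of EPDS thresholds, because EPDS is the primary outcome and no interim analysis is planned.
3. In the final report, tabulate them by arm, with the number of women answering at each timepoint as denominator for the survey items.
4. List volunteered reports separately, and say that they were spontaneous and unblinded.

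The cost is a few extra record-extraction fields and one table; no new survey is needed. Pooled counts will not show the DMC an imbalance between arms during the trial. That is the price of keeping the primary outcome unexamined by arm until the end.

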### Frequency and plans for auditing trial conduct {23}

The Project Steering Committee and research team will meet every 3 months to review the progress and conduct of the trial. Annual reports will be submitted to the funding body.

### Plans for communicating important protocol amendments to relevant parties (e.g. trial participants, ethical committees) {25}

Protocol amendments will first be submitted to the Mater Human Research Ethics Committee for approval. If any changes are made that may in any way affect participants’ participation activities, involvement, or consent processes, participants will be informed of these changes by a member of the research team by email or phone.

## Dissemination plans {31a}

The authors will disseminate the results of the study at conferences and by publication in peer-reviewed journals.

## Discussion

Following the conclusion of this RCT, our results will inform the wider implementation and scalability of the app for use in other maternity services and other services across the continuum of perinatal mental health care, both nationally and internationally. This intervention can also be applied to partners and family members, as well as more vulnerable populations (e.g. women with high-risk pregnancies, increased childbirth fear, or perinatal mental illnesses). The cost-effectiveness evaluation will highlight any financial benefits of employing the app in current services.

A cost-effective or cost-saving mobile app intervention that improved mother-infant bonding and/or reduced postnatal depression would have wide-ranging benefits for healthcare services and patients. An online service would be accessible to previously inaccessible rural and remote patients or patients unable to leave the home due to health concerns or family commitments. Reductions in healthcare visits would also benefit patients in terms of the financial and time commitments necessary to travel to healthcare appointments. Reductions in postnatal depression would reduce ED presentations and therefore financial costs to the healthcare system [32]. Our cost-effectiveness evaluation will estimate these financial benefits.

## Trial status

Protocol version 3.1 (5 September 2022) was approved by the Mater Ethics Committee on 17 October 2022 (Ref: AM/MML/83589 (V3)). Recruitment for the trial will begin in November 2023 and will be completed by July 2024.

## Data Availability

Access to study data may be given upon request to the corresponding author.

## Abbreviations

ED: Emergency department
QALY: Quality-adjusted life years
RCT: Randomised controlled trial
